## Abstract

**Objective:**

Low anterior resection syndrome (LARS), a prevalent sequela following rectal cancer surgery, poses a substantial burden on patients’ quality of life (QOL), daily functioning, and psychological well-being, and its management remains an unmet clinical need due to the absence of specific therapeutic agents. Although traditional Chinese medicine (TCM) shows promise in supporting postoperative gastrointestinal recovery, high-quality evidence for its application in LARS is lacking. This trial is designed to assess the efficacy and safety of the investigational TCM formulation BL-1 in patients with LARS.

**Methods/design:**

The study will be conducted as a randomized, double-blind, placebo-controlled trial, comprising a 4-week intervention phase and a subsequent 2-week follow-up period. A total of 234 patients with LARS, aged 18 to 75 years, are planned to be enrolled in this study. Eligible participants will be randomized to receive either the BL-1 group or placebo group in a 1:1 ratio. Participants in the experimental group will receive BL-1 formulation, whereas those in the placebo group will receive an indistinguishable BL-1 placebo. The primary outcome measure is the change in LARS score from baseline to week 4. Secondary outcome measures encompass: (a) stool frequency and consistency (assessed via the Bristol Stool Scale); (b) severity of fecal incontinence (evaluated using the Wexner Anal Incontinence Scale); (c) QOL, measured with the European Organization for Research and Treatment of Cancer QOL questionnaire and the Karnofsky Performance Status score; and (d) other patient-reported outcomes. Safety will be monitored continuously throughout the treatment, with assessments including the incidence of adverse events and laboratory abnormalities.

**Discussion:**

BL-1 is the compound prescription of eleven traditional Chinese medicinal materials: Bupleuri Herba, Ginseng Radix et Rhizoma, Astragali Radix, Atractylodis Macrocephalae Rhizoma, Cimicifugae Rhizoma, Mume Fructus, and Aconiti Lateralis Radix Praeparata (patent number ZL 2024 1 1479878.8). In recent years, BL-1 has been applied to treat digestive system diseases, particularly defecation disorders, and may offer potential benefits for adults with LARS. The absence of robust clinical evidence has prompted the design of this randomized, double-blind, placebo-controlled trial to rigorously evaluate its therapeutic efficacy and safety. This trial is expected to yield critical data that will inform the clinical use of BL-1 formulation in the management of LARS.

**Ethics and dissemination:**

Ethical approval for this study was obtained from the Ethics Committee of West China Hospital, Sichuan University (Approval ID: 20241218). All participants must provide written informed consent before randomization. Subsequently, the trial results will be submitted for publication in a peer-reviewed academic journal.

**Clinical trial registration:**

https://www.chictr.org.cn, identifier ChiCTR2400087108.

## Introduction

1

Colorectal cancer is the third most commonly diagnosed cancer globally, with nearly 50% of these cases originating in the rectum (1). According to the statistics of the China Cancer Centre, the fatality rate of colorectal cancer ranks fourth, and the incidence rate continues to increase (2). Current management of rectal cancer primarily relies on surgery, with sphincter-preserving techniques being highly prioritized provided that oncological outcomes are not compromised. Low anterior resection and/or total mesorectal excision are the preferred surgical methods for radical resection of low rectal cancer because the can avoid the need for a lifelong stoma (3, 4). This intervention, however, induces significant alterations in anorectal physiology, giving rise to a spectrum of defecatory abnormalities collectively referred to as low anterior resection syndrome (LARS). With an incidence ranging from 25% to 80%, this syndrome manifests predominantly as fecal incontinence, defecatory urgency, and elevated bowel movement frequency (5). While some symptomatic improvement may occur between 6 months and 1 year postoperatively (6, 7), a majority of patients continue to experience long-term disordered bowel function after rectal resection. These persistent alterations commonly include unpredictable bowel habits, changes in stool consistency, increased frequency, painful defecation, emptying difficulties, urgency, incontinence, and soiling (8). These defecatory problems represent a primary source of patient distress post-surgery and substantially compromise overall quality of life (QOL) (9, 10).

The etiology and pathogenesis of LARS are multifactorial, primarily involving three interrelated mechanisms. (1) the neorectum’s impaired reservoir function leads to reduced storage capacity. (2) direct injury to the anal sphincter complex or its innervation during surgical dissection or anastomosis is a critical determinant. (3) preoperative radiotherapy and postoperative complications (e.g., anastomotic leakage) further contribute to the symptomatic spectrum (11). The underlying pathogenesis of LARS encompasses several physiological disturbances, such as internal anal sphincter dysfunction, diminished rectal sensitivity and compliance, and the loss of the rectoanal inhibitory reflex (11). Disruption of the pelvic neural plexus during low anterior resection may result in aberrant reinnervation of the neorectum, a process that can contribute to the exacerbation of LARS symptoms (12). However, current therapies, including diet and lifestyle modifications, pelvic floor muscle training, transanal irrigation, antidiarrheal drugs, 5-hydroxytryptamine (5-HT) receptor antagonists, fiber, probiotics and even neuromodulation, are not always effective (9, 11). The high incidence of rectal cancer in our country underscores the urgency for developing safe and effective pharmacological interventions for LARS, which would hold substantial clinical and societal value.

While LARS is not a defined disease entity in Traditional Chinese Medicine (TCM), its clinical manifestations can be understood and categorized within TCM theory primarily as patterns of diarrhea and constipation, based on the predominant symptoms. Modern surgical removal of cancerous tumors falls under the category of ‘eliminating pathogens’ (addressing symptoms), but the pathological mechanism of LARS, ‘spleen qi deficiency’ (the root cause), persists throughout patients at different stages and severity levels. (1) Weakness of the spleen and stomach leads to sinking of clear yang and inadequate lifting, resulting in rectal prolapse and incontinence; (2) deficiency of yang energy in the large intestine results in dysfunctional fecal discharge, primarily presenting as incomplete defecation. TCM offers a comprehensive therapeutic system for managing LARS, which includes internal and external methods. The TCM management strategy incorporates both external methods (such as electroacupuncture, external application, and moxibustion) and internal approaches (primarily involving oral traditional Chinese herbal formulas and oral Chinese patent medicines). Previous studies have shown that the Chinese herbal formulas Buzhong YiQi (13, 14) and Shenling Baizhu San (15) can improve LARS symptoms in patients after low anterior resection of rectal cancer in the short term. However, studies published to date have small sample sizes, and a high proportion of clinical trials were conducted with nonrandomized designs in, which limits the generalizability of the clinical findings of these studies for the above Chinese herbal compound formulas.

BL-1 is a proprietary herbal formulation developed by West China Hospital of Sichuan University. Our team’s preliminary small-sample pilot study results indicate that BL-1 has an efficacy rate of approximately 65% in treating LARS (data not yet published). It contains various key components, including but not limited to Bupleuri Herba, Ginseng Radix et Rhizoma, Astragali Radix, Atractylodis Macrocephalae Rhizoma, Cimicifugae Rhizoma, Mume Fructus, and Aconiti Lateralis Radix Praeparata (patent number ZL 2024 1 1479878.8). BL-1 aims to treat the root-cause of LARS with “sun-uplift and dispel cold and dampness” and its symptoms with “astringent intestines and stop”. This formulation is particularly suitable for LARS patients diagnosed with “Yangming deficiency cold syndrome”, especially those with urgent fecal incontinence. Consequently, a randomized, multiple-blind, placebo-controlled trial is designed to assess the efficacy and safety of BL-1 formulation for treating adults with fecal incontinence-type LARS.

## Methods/design

2

### Study design

2.1

This study is a multicenter, randomized, double-blind, placebo-controlled exploratory trial. The protocol was developed in accordance with the Standard Protocol Items: Recommendations for Interventional Trials guidelines (16). **Figure 1** presents the trial timeline and assessment schedule. Eligible participants will be randomized to receive either the BL-1 formulation or placebo at a 1:1 ratio. The trial for both groups will comprise a 4-week intervention period followed by a 2-week follow-up. Ethical approval was obtained from the Ethics Committee of West China Hospital, Sichuan University (Approval ID: 20241218). The trial was prospectively registered in the Chinese Clinical Trial Registry under the identifier ChiCTR2400087108.

**Figure 1 f1:**
[figure not shown]
SPIRIT schedule. Blood tests or verify results are required during the Preparation period BL-1, a proprietary herbal formulation developed by West China Hospital of Sichuan University; LARS, low anterior resection syndrome; EORTC QLC-CR30, the scale of cancer-specific European Organization for Research and Treatment of Cancer; AFT, prior to the initiation of therapy.

### Trial status

2.2

The protocol has been updated to version V4.1.1 (revised October 2025). To date, 92 participants have been enrolled, with completion anticipated by June 2027. The study results are expected to be published in December 2027.

### Trial setting

2.3

We will recruit 234 LARS patients from the outpatient clinic or inpatient ward of hospitals in Chengdu, China: West China Hospital of Sichuan University, Sichuan Cancer Hospital, and the Affiliated Hospital of Chengdu University of Traditional Chinese Medicine.

### Participants

2.4

#### Recruitment

2.4.1

Recruitment strategies will include hospital social media (e.g., WeChat subscriptions), digital posters (e.g., WeChat Moments), on-site postings in outpatient clinics and wards, as well as advertisements in surrounding community service centers: 1) the recruitment posters (both print and electronic) will outline the key eligibility criteria for potential participants and provide details regarding the trial activities and commitments involved; 2) in clinical settings (outpatient and inpatient), physicians will initially identify potential candidates suspected of having LARS for a subsequent detailed evaluation to determine final eligibility. Simultaneously, we will provide contact information for participants as well as gastroenterologists and gastrointestinal surgeons. The Clinical Research Coordinator will evaluate the eligibility of potential participants through post-surgical interviews, applying the study’s inclusion and exclusion criteria. All included patients or their legally authorized representatives will voluntarily agree to participate and will sign an informed consent document before randomization; 3) participant adherence will be enhanced through a strategy of regular telephone follow-ups.

#### Participant inclusion criteria

2.4.2

The key inclusion criteria are as follows: (a) aged 18–75 years; (b) a preoperative clinical diagnosis of rectal cancer with a TNM stage I–III; (c) patients meeting the 2020 LARS diagnostic criteria with a LARS score ≥ 20; (d) transanal defecation frequency ≥ 4 times/day; (e) rectal cancer anal sphincter preservation surgery (including preventive stoma retraction surgery) performed at least one month prior; (f) a Karnofsky score > 60 and an expected survival > 6 months; (g) patients with basic communication skills and understanding who are willing to cooperate with the examination, treatment and follow-up; and (h) patients who have provided signed informed consent following a detailed explanation of the trial.

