#### Primary outcomes

2.7.1

The primary outcome is defined as the change in LARS score between baseline and week 4. The degree of LARS symptom severity will be measured using the LARS symptom severity score (LARSS) (20). The LARSS is assessed across five key domains: incontinence for flatus, incontinence for liquid stool, stool frequency, clustering of bowel movements, and urgency. The summation of individual item scores yields the total score, which is subsequently categorized according to predefined severity levels. The LARSS will be used to stratify disease severity into three levels: normal (score ≤ 20), mild (21 ≤ score ≤ 29), and severe (30 ≤ score ≤ 42). Treatment response will be evaluated based on changes in severity from original (baseline) level. Patients showing no improvement or any deterioration (e.g., from mild to severe) will be classified as non-responders, while those demonstrating improvement will be categorized as responders (e.g., from severe to mild, from severe to normal, and from mild to normal). The response rate is defined as the ratio of responding participants to the total number of randomized participants, multiplied by 100%.

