#### Secondary outcomes

2.7.2

Secondary endpoints will include the following: (a) changes in the LARSS from baseline to weeks 2 and 6; (b) the proportion of patients demonstrating improvement in bowel dysfunction across the three assessment time points (weeks 2, 4, and 6). Clinical transitions in LARS severity will be assessed using the LARSS, specifically documenting the number of patients transitioning from severe to mild, mild to none, and severe to none; (c) stool frequency, which will be assessed by recording the average number of spontaneous bowel movements per day or per week for the patients at weeks 0, 2, 4, and 6; (d) stool consistency, which will be assessed by recording the average daily or weekly stool consistency at weeks 0, 2, 4, and 6 (21); (e) anal function, which will be assessed using the Wexner anal incontinence scale score at weeks 0, 2, 4, and 6 (22); (f) QOL, which will be assessed at weeks 0, 4, and 6 using the cancer-specific European Organization for Research and Treatment of Cancer scale (EORTC QLQ-C30) (23); (g) functional status, which will be assessed using the Karnofsky Performance Status (KPS) score at weeks 0 and 4; and (h) safety, which will be evaluated as follows: 1) biochemical indices, including liver function (alanine aminotransferase and aspartate aminotransferase), kidney function (blood urea nitrogen and creatinine); 2) electrocardiographic assessment of cardiac electrical activity; 3) adverse events (AEs): any unfavorable symptoms (including rash, constipation) documented during treatment. AE incidence: (number of patients experiencing AEs/total number of patients) × 100%; 4) severe AEs.

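### A patient can enter with a LARS score of 20, which the outcome bands call normal, and can then never count as a responder (minor; response-rate endpoints only)

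*Protocol article*

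**What the plan says.** - Section 2.4.2, criterion (c), sets the score needed for entry: "patients meeting the 2020 LARS diagnostic criteria with a LARS score ≥ 20". The value 20 is included.
- Section 2.7.1 names the continuous primary outcome: "The primary outcome is defined as the change in LARS score between baseline and week 4".
- The same section then bands the score as "normal (score ≤ 20), mild (21 ≤ score ≤ 29), and severe (30 ≤ score ≤ 42", and bases response on the bands: "Treatment response will be evaluated based on changes in severity from original (baseline) level".
- Non-response is defined by "Patients showing no improvement or any deterioration (e.g., from mild to severe) will be classified as non-responders". The responder moves listed are "e.g., from severe to mild, from severe to normal, and from mild to normal", and none of them starts from normal.
- The response rate is "the ratio of responding participants to the total number of randomized participants, multiplied by 100" (as a percentage), so no randomized patient is left out of the denominator.
- Section 2.7.2(b) uses the same moves at weeks 2, 4 and 6, "specifically documenting the number of patients transitioning from severe to mild, mild to none, and severe to none".
- Section 2.11 prespecifies a subgroup analysis by baseline LARS severity, without listing its levels.

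**The concern.** The entry range and the normal band share one value, 20. A patient with that baseline already sits in the best band, the one the trial treats as full success for everyone else. No better band exists, so the response rule counts this patient as a failure whatever happens on treatment, even if the score falls to 0. Nothing in the article removes such patients from the denominator or gives them another way to respond.

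Three things are at stake: the size of the response rate in each arm, the between-arm difference on the response and transition endpoints, and the baseline-severity subgroup, which would acquire a level that patients treated for LARS would not be expected to occupy.

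**Working it through.** **Step 1. The plan's own figure.** Section 2.8 gives mean reductions of 9.75 and 8.55 (difference 1.20), SD 2.5, two-sided α = 0.05 and power 0.90.

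- Normal approximation: n = 2(1.960 + 1.282)² × 2.5² / 1.20² = 91.2, so 92 per group.
- Two-sample t-test: 92.18, so 93 per group, as stated.
- Withdrawal of 20%: 93 / 0.80 = 116.25, so 117 per group and 234 in total, as stated.

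The calculation rests on the change in score. A patient who enters at 20 can still change score, so this point does not alter the sample size.

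**Step 2. Which final scores count as a response.** Each possible final score from 0 to 42 was compared with the baseline band.

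| Baseline score | Baseline band | Final scores that count as response |
|---|---|---|
| 20 | normal | none |
| 21 or 29 | mild | 0 to 20 (21 values) |
| 30 or 42 | severe | 0 to 29 (30 values) |

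For a baseline of 20 the probability of response is 0 in both arms.

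**Step 3. Dilution.** Let f be the share of randomized patients at 20, and p the response rate among the rest. The reported rate is then (1−f)p and the ceiling is 1−f. With the same expected f in each arm, the difference also becomes (1−f) times its value among the rest. The article does not give f, so a range is assumed. The illustrative p is the approximate 65% efficacy rate that the Introduction reports from the pilot study.

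| Assumed f | Patients per arm (of 117) | Ceiling | 65% becomes |
|---|---|---|---|
| 0% | 0 | 100% | 65.0% |
| 2% | 2.3 | 98% | 63.7% |
| 5% | 5.9 | 95% | 61.8% |
| 10% | 11.7 | 90% | 58.5% |
| 20% | 23.4 | 80% | 52.0% |

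**Step 4. Effect on the between-arm difference, under one assumed baseline.** Assume that baseline is uniform over the 23 integers from 20 to 42. Then f = 1/23 = 4.3%, and 0.043 × 234 is about 10 patients. Assume also that reductions are normal with the section 2.8 means and SD. For baseline b above 20, let t be the highest score in the next better band (20 if mild, 29 if severe). The response probability is P(reduction ≥ b − t), averaged over b. Scores are integers, so the result is shown with and without a half-point continuity correction.

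| | Baseline 21–42 only | Baseline 20–42 |
|---|---|---|
| No correction: BL-1 | 78.7% | 75.3% |
| No correction: placebo | 70.4% | 67.4% |
| No correction: difference | 8.3 points | 7.9 points |
| Half-point correction: BL-1 | 81.7% | 78.2% |
| Half-point correction: placebo | 74.0% | 70.8% |
| Half-point correction: difference | 7.7 points | 7.4 points |

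The levels depend on the correction, but the shrinkage hardly does. It is (8.3 / 23) ≈ 0.36 points without the correction and (7.7 / 23) ≈ 0.33 points with it.

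**The case against.** The strongest reply is that this hardly matters, and most of that reply stands. The primary outcome is a continuous change, to which a patient at 20 contributes fully. The share at 20 may be nil. Under the uniform assumption the difference moves by less than half a point, and with modelled response rates of about 70% to 82% a ceiling a few points below 100% has little practical force. Randomization spreads such patients evenly in expectation, so the effect is dilution and not bias towards either arm.

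A reader might also infer four stronger things that the protocol does not support:

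- **That such patients do not have LARS.** Criterion (c) also requires the 2020 diagnostic criteria, and criterion (d) requires at least 4 defecations a day. The Discussion describes the consensus definition by symptoms and consequences, with no score cut-off. The conflict is between an entry definition and a band label.
- **That they have no place in the severity subgroup.** Section 2.7.1 defines three levels, so they would form a normal stratum, probably too sparse to interpret.
- **That the entry threshold is the error.** The article does not show whether the threshold or the edge of the band is the slip.
- **That the primary analysis or the sample size is compromised.** Step 1 of the working shows that neither is touched.

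What the reply does not remove is the contradiction. The thresholds, the response rule and the denominator are all printed in the article, and together they give a patient at 20 a fixed outcome.

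**Conclusion.** The point holds as a minor internal inconsistency. Sections 2.4.2 and 2.7.1 overlap at a score of 20, and any patient entering there is a non-responder by rule in both arms. The response rate in section 2.7.1 is multiplied by 1−f. The improvement proportion in section 2.7.2(b) is affected in the same way if it uses the same denominator, which that section does not restate.

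The size rests on f, which is unknown. It is zero if nobody enters at 20. It is about 4%, with a loss of 0.3 to 0.4 points in the between-arm difference, if baseline is uniform over 20 to 42 and reductions follow the planning values. That uniform baseline is an assumption made here and has no source in the protocol.

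**What to change.** 1. Reconcile criterion (c) with the bands in section 2.7.1 so that no score both qualifies for entry and counts as normal. If the bands stand, entry at 21 or more would do this. Which of the two to change is for the sponsor to decide.
2. Before unblinding, add a sentence on anyone already randomized with a baseline of 20: they stay in the change-score analysis, and the response rate and severity transitions are calculated among patients with a mild or severe baseline. The restriction uses a baseline value only, so it preserves the randomized comparison. If it were settled after unblinding, the choice of denominator could look data-driven.
3. State that the baseline-severity subgroup compares mild with severe.

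**Cost.** The edits are short, but item 2 changes the all-randomized denominator stated in section 2.7.1 and should say so openly. Section 2.12 requires approval by the principal investigators, ethics re-approval and a registry update, and section 2.2 reports 92 of the planned 234 participants already enrolled. If the entry threshold is the part that changes, a few otherwise eligible patients may be lost. The sample size stays the same.

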#### Participant exclusion criteria

2.4.3

The exclusion criteria are as follows: (a) patients undergoing postoperative radiotherapy and chemotherapy; (b) patients with an established etiology for diarrhea other than LARS (e.g., Crohn’s disease, irritable bowel syndrome, or other known causes); (c) patients with local tumor recurrence; (d) patients with the presence of serious postoperative complications, exemplified by anastomotic leakage or stenosis; (e) patients with concomitant liver dysfunction (alanine aminotransferase or aspartate aminotransferase exceeding 1.5 times the upper limit of normal) and renal dysfunction (chronic kidney disease stage 4 or above); (f) patients with severe brain, heart, and other systemic diseases; (g) individuals with neurological or mental disorders who are unable or unwilling to cooperate; (h) patients with legally defined disabilities (e.g., visual/hearing/speech impairment or intellectual disability); (i) individuals suspected or confirmed to have a recent history of alcohol abuse, drug misuse, or illicit substance use; (j) pregnant or lactating women or individuals with a near-term pregnancy plan; and (k) those who have been treated with TCM during the past 3 months or who have participated in other clinical trials.

